### Data collection methods

All data will be collected following standardised operating procedures to ensure validity, reproducibility and compliance with GCP. Physiological assessments, including tilt testing, ECG, BP, RSA and capnography, will be conducted by a trained study nurse in accordance with the predefined test protocol. The study nurse will receive specific training in autonomic testing and laboratory safety before the trial begins to ensure consistent assessment practices. Patient-reported outcomes will be gathered using validated and widely recognised questionnaires: the NQ, BPAT, MAPS, SF-12, CFS, HADS. Questionnaires will be provided either in paper format or digitally, depending on participant preference and health condition. To improve data quality, the study nurse will perform immediate plausibility checks of recorded measurements and questionnaires after each visit. All data will be documented in electronic case report forms via REDCap. Range checks and automatic validation rules will be implemented to minimise data entry errors. Paper forms will be available as a backup in case of system failure and will be double-entered into REDCap as soon as possible.

### Plans to promote participant retention and follow-up

During the 12-week intervention, the study nurse will maintain regular contact with participants through phone calls at weeks 2, 6 and 10, as well as email reminders. Participants will also receive text messages or emails 48–72 hours prior to each scheduled visit. If an appointment is missed, an immediate phone call will be made to reschedule and record the reason for non-attendance. Participants who discontinue the intervention will be encouraged to continue participating in follow-up assessments to collect primary and secondary outcome data. If on-site testing is not possible, questionnaire and safety data will be gathered via phone or online survey. All reasons for discontinuation will be documented. The intention-to-treat analysis will include participants with partial outcome data, where feasible.

### Data management

All trial data will be entered into REDCap, a GCP-compliant, password-secured electronic database hosted on secure institutional servers at the Medical University of Vienna. Access will be role-restricted (study nurse, PI, statistician) and all activities will be logged with an audit trail. Data will be anonymised by assigning unique participant identifiers; personal identifiers will be stored separately from trial data. Quality control will include range checks, consistency checks and double data entry for critical variables. Weekly backups will be performed automatically on institutional servers. Only authorised study team members will have access to the final dataset. After study completion, both electronic and paper records will be archived for 15 years in accordance with Austrian General Data Protection Regulation (GDPR).

### Statistical methods

Statistical analyses will be conducted using IBM SPSS Statistics version 28.0 for Windows (IBM). Continuous variables will be expressed as mean±SD deviation (SD), while categorical variables will be shown as frequencies and percentages with 95% CIs. The primary endpoint, HR change (ΔHR), defined as the difference between upright and supine HR, will be analysed using repeated-measures ANOVA with Bonferroni correction applied to account for multiple comparisons. The main comparison will focus on the change in ΔHR from baseline to week 12 across the four intervention groups. Exploratory secondary analyses will examine changes in BP, HRV, RSA, handgrip strength and patient-reported outcomes (MAPS, CFS, SF-12, HADS). For these outcomes, linear regression models incorporating baseline values, age, sex and medication as covariates will be employed. Interaction terms for time-by-group will be included to identify potential differences in trajectories over time. Assumptions of normality and homoscedasticity will be assessed with QQ-plots and residual plots. When appropriate, non-parametric methods will be used for sensitivity analyses. Analyses will follow the intention-to-treat principle, including all randomised participants according to their allocated intervention group, regardless of adherence or protocol deviations. An additional per-protocol analysis will be performed as a sensitivity check, limited to participants with ≥80% adherence to the intervention protocol. Missing data will be addressed through multiple imputation under the assumption of missing at random. Sensitivity analyses will also be conducted using last observation carried forward and complete-case analysis to evaluate robustness. Regarding the results, study nurses will systematically document reasons for missing data in the case report forms. All confirmatory tests for the primary outcome will be two-sided, with a significance level set at α=0.05, adjusted for multiple comparisons using Bonferroni correction. P values from secondary analyses will be considered exploratory and interpreted accordingly.

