### Objectives

The main aim is to assess whether 12 weeks of AVNT combined with SDB (AVNT+SDB) produces a greater improvement in autonomic function, measured as a reduction in the orthostatic HR change (ΔHR) during a standardised 70° head-up tilt, than AVNT+NB, sham AVNT+SDB or sham AVNT+NB. ΔHR is predefined as the mean HR during the 10-minute upright head-up tilt phase minus the mean HR during the 10-minute supine baseline period; comparisons between AVNT+SDB and each other group are confirmatory, while all other pairwise comparisons are exploratory.

Secondary objectives include characterising between-group differences in beat-to-beat BP responses (mean arterial pressure (ΔMAP), systolic BP (ΔSBP), diastolic BP (ΔDBP), the initial orthostatic nadir, and time to recovery). Respiratory sinus arrhythmia (RSA) is assessed as an index of cardiac vagal modulation using ECG-derived HR variability (HRV), assessing patient-reported outcomes using the Short Form Health Survey (SF-36) for health-related quality of life, the Hospital Anxiety and Depression Scale (HADS) for symptoms of anxiety and depression, Chalder Fatigue Scale (CFS), the Malmö POTS Symptom Score (MAPS) and the Nijmegen Questionnaire (NQ) for symptoms of dysfunctional breathing.

As a safety objective, the trial will evaluate tolerability and systematically record adverse events (AEs) and serious AEs (SAEs), including treatment-related discontinuations, throughout the study, with descriptive comparisons of event profiles across the four groups.

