### Sample size calculation

As no study has yet defined the minimal clinically important difference for HR reduction in POTS, we consider the results of Stavrakis *et al*^20^ to be clinically relevant and have therefore used them as the basis for our sample size calculation. In addition, in the absence of direct clinical data on the effect of slow breathing training on POTS, we assumed an additional reduction from slow breathing training based on studies showing that slow breathing training can reduce HR by approximately 4–10 bpm in various cardiovascular conditions.^34 39 40^ We have used a conservative estimate of seven beats per minute, which we believe to be a minimal clinical difference. This reduction represents not only a measurable physiological change but may also contribute to psychological well-being, as studies suggest.^41^ For our clinical trial investigating the effects of AVNT with and without breathing training and a sham AVNT intervention, we calculated the required sample size based on expected HR changes (ΔHR). This calculation was performed for an analysis of variance using HR data from Stavrakis *et al*^20^ and incorporating an assumed reduction of 7 bpm from slow breathing. Although Stavrakis *et al*^20^ reported no significant reduction in HR in the sham AVNT group, we conservatively assumed a placebo-related reduction of 2 bpm for both sham conditions to account for potential expectancy effects.

We estimated the following mean ΔHR values across the four groups:

AVNT with NB: 17.6 bpm (as reported by Stavrakis *et al*)^20^AVNT with slow-paced breathing: 10.6 bpm (17.6–7 bpm)Sham AVNT with slow-paced breathing: 22.7 bpm (placebo-adjusted 2 bpm reduction from 31.7 and 7 bpm reduction from slow-paced breathing)Sham AVNT with NB: 29.7 bpm (placebo-adjusted 2 bpm reduction from 31.7 bpm)

Assuming an SD of 14 bpm, an alpha level of 0.0167 (Bonferroni correction for 3 pairwise comparisons across four groups), and a power of 80%, 17 participants per group are required for sufficient statistical power. To account for an anticipated 30% dropout rate, 25 participants per group will be recruited, resulting in a total sample size of 100 participants.

Sample size was computed using the University of Vienna’s online analysis of variance (ANOVA) calculator: https://homepage.univie.ac.at/robin.ristl/samplesize.php?test=anova

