#### Type of randomisation

Stratified block randomisation with a 1:1:1:1 allocation ratio will be used across the four study groups: AVNT+SDB, AVNT+NB, sham AVNT+SDB and sham AVNT+NB. Randomisation will be stratified by PEM status (yes/no), resulting in two strata. The precise block sizes and restrictions are programmed within the Randomiser system but remain undisclosed to the investigators to minimise predictability.

Sex distribution will be monitored throughout recruitment and reported descriptively. Given the expected limited number of male participants, additional stratification by sex was not implemented, as this could result in small and unstable subgroups. However, sex will be considered in the statistical analysis as a covariate or explored in sensitivity analyses, where sample size permits.

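### The primary ΔHR analysis is an unadjusted change-score comparison; ANCOVA on baseline ΔHR and the PEM stratum would be more precise at almost no cost

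*Protocol article*

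**What the plan says.** The Statistical methods section states that ΔHR "will be analysed using repeated-measures ANOVA with Bonferroni correction applied to account for multiple comparisons". It then sets the focus: "The main comparison will focus on the change in ΔHR from baseline to week 12 across the four intervention groups". No covariate is named for this model. For the exploratory outcomes the same section plans linear regressions adjusted for the outcome's baseline value, age, sex and medication.

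Under Type of randomisation: "Randomisation will be stratified by PEM status (yes/no), resulting in two strata". PEM is in neither covariate description. That section adds that sex will be a covariate or the subject of sensitivity analyses if numbers allow.

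The confirmatory family is set out in the Objectives: "comparisons between AVNT+SDB and each other group are confirmatory, while all other pairwise comparisons are exploratory". The Sample size calculation uses "an alpha level of 0.0167 (Bonferroni correction for 3 pairwise comparisons across four groups", and Statistical methods confirms the family level: "All confirmatory tests for the primary outcome will be two-sided, with a significance level set at α=0.05, adjusted for multiple comparisons using Bonferroni correction".

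**The concern.** Subtracting the baseline fixes its coefficient at 1. Unless baseline and week-12 values are perfectly correlated, that is not the best coefficient, and the excess goes into the error term. ANCOVA estimates the coefficient from the data. As written, the one confirmatory endpoint gets a less efficient analysis than the exploratory outcomes.

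The second point is the stratum. Stratified randomisation balances PEM across arms. If PEM predicts the outcome and is left out of the model, the variance it explains stays in the error term and the standard errors are too wide.

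At stake is power for the comparisons with AVNT+NB and sham AVNT+SDB, which have little of it to lose.

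**Working it through.** **Inputs from the article.** Expected ΔHR: AVNT+SDB 10.6, AVNT+NB 17.6, sham+SDB 22.7, sham+NB 29.7 bpm. "Assuming an SD of 14 bpm"; alpha 0.0167; "a power of 80%, 17 participants per group are required for sufficient statistical power"; 30% dropout.

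**Inputs assumed.** The correlation ρ is not given, so a range is shown. SD 14 is taken as the SD of ΔHR at each visit. The article does not say so, but its planning means are ΔHR levels rather than changes.

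**The plan's own figure.** An omnibus one-way ANOVA F test with these means, SD 14 and alpha 0.0167 needs 16 per group (power 0.820). The stated 17 gives 0.851, so the figure is reproduced to within one participant per group. Dropout: 17/0.70 = 24.3, rounded up to 25, as stated.

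**Step 1: equivalence.** In a simulated data set with four arms and two visits, the group-by-time F and the one-way ANOVA F on change scores were both 3.3318.

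**Step 2: variances.** With common SD σ at both visits:
- change score: 2(1−ρ)σ²
- ANCOVA residual: (1−ρ²)σ²
- ratio, ANCOVA to change: (1−ρ²)/[2(1−ρ)] = (1+ρ)/2

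The ratio is 0.65 at ρ = 0.3, 0.75 at 0.5, 0.85 at 0.7 and 0.95 at 0.9. If the SDs differ (σ₀ at baseline, σ₁ at week 12), the change-score variance minus the ANCOVA variance is σ₀² + σ₁² − 2ρσ₀σ₁ − (1−ρ²)σ₁² = (σ₀ − ρσ₁)², which is never negative.

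With σ = 14, the change-score SD is 14√1.4 = 16.6, 14√1.0 = 14.0 and 14√0.6 = 10.8 at ρ = 0.3, 0.5 and 0.7. The ANCOVA SD is 14√0.91 = 13.4, 14√0.75 = 12.1 and 14√0.51 = 10.0. So the change-score SD is above 14 when ρ is below 0.5, and below 14 when ρ is above 0.5.

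**Step 3: power of the three contrasts.** The differences from AVNT+SDB are 17.6 − 10.6 = 7.0, 22.7 − 10.6 = 12.1 and 29.7 − 10.6 = 19.1 bpm. Standard error = SD × √(2/17). Power is from the noncentral t at two-sided 0.05/3, with 68 − 4 = 64 error df for the change score and 68 − 6 = 62 for ANCOVA with baseline and PEM.

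| ρ | 7 bpm (vs AVNT+NB): change → ANCOVA | 12.1 bpm (vs sham+SDB) | 19.1 bpm (vs sham+NB) |
|---|---|---|---|
| 0.3 | 0.117 → 0.184 | 0.378 → 0.574 | 0.814 → 0.953 |
| 0.5 | 0.166 → 0.227 | 0.528 → 0.673 | 0.932 → 0.982 |
| 0.7 | 0.290 → 0.345 | 0.784 → 0.854 | 0.996 → 0.999 |

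The ANCOVA column leaves out the small cost of chance baseline imbalance. Simulation with baseline as covariate (8,000 runs) gave 0.558, 0.661 and 0.850 for the 12.1 bpm contrast, so the table is up to about two points generous.

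**Step 4: leaving out PEM.** The article gives neither the prevalence nor the prognostic effect of PEM. With an assumed 50% prevalence, blocks of four, 25 per arm and nominal size 0.0167 (4,000 runs), the unadjusted test had size 0.0085 for a 14 bpm PEM effect and 0.0035 for 21 bpm, against 0.0168 with adjustment in both cases. With 7 bpm or no effect there was no clear difference. Any error is in the conservative direction.

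**The case against.** The strongest reply is that nothing here is wrong. A change-score analysis in a randomised trial is unbiased and keeps its type I error. The size of the gain rests on two things the article does not state: ρ, and what SD 14 describes. At ρ = 0.9 the variance saving is only 5%. All of this stands, and it limits the point to efficiency. It does not remove it, because the method is a stated choice and the direction of the gain does not depend on ρ.

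A reader might infer more, in four ways that the article does not support.

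- **That the three contrasts are not planned, or that Bonferroni might run over all six pairs.** Objectives names three confirmatory contrasts and makes the rest exploratory, and the Sample size calculation sets 0.0167 for three comparisons. Statistical methods does not repeat the number, but read together the sections are clear.
- **That the plan excludes PEM.** It is silent. The article is condensed, an analysis plan may exist, and the remark on sex under Type of randomisation shows that Statistical methods is not the full covariate statement. PEM is therefore the weaker half of the point, and its gain cannot be quantified.
- **That Bonferroni is a fault.** It is valid, prespecified and matches the sample-size alpha. Holm would add power, not precision, at the same family-wise error: with ANCOVA at ρ = 0.5 the 7 bpm contrast goes from 0.226 to 0.356, with simulated family-wise error 0.040 for both under the global null. But Holm has no simple matching simultaneous confidence intervals.
- **That adjustment repairs the trial's power.** The 17 per group comes from an omnibus test, and no covariate makes that enough for a 7 bpm contrast.

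**Conclusion.** The point holds as a matter of efficiency, not validity. The stated primary analysis is a change-score ANOVA with no named adjustment for baseline ΔHR or the randomisation stratum. ANCOVA would reduce the variance by 35% to 15% for ρ between 0.3 and 0.7. At 17 per arm this adds about 20, 15 and 7 percentage points of power for the 12.1 bpm contrast at ρ = 0.3, 0.5 and 0.7, and about 6 points for the 7 bpm contrast, which still reaches at most 35% over that range.

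This rests on an assumed ρ, a common SD of 14 at each visit, and two occasions; the last is taken from Statistical methods, because the visit schedule figure is not shown. If SD 14 is instead the SD of the change, the change-score powers are those of the ρ = 0.5 row whatever ρ is, and ANCOVA still has (1+ρ)/2 of that variance. Leaving out PEM, if it is prognostic, costs power and does not inflate type I error; by how much is unknown.

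**What to change.** Amend the primary analysis to an ANCOVA of week-12 ΔHR on baseline ΔHR, PEM stratum (yes/no) and randomised arm. State in Statistical methods that the confirmatory tests are the three contrasts of AVNT+SDB with each other arm, at the prespecified Bonferroni level of 0.05/3, with matching confidence intervals. Keep the repeated-measures ANOVA as a sensitivity analysis. Holm may be considered as an option, with its interval limitation stated.

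The cost is one error degree of freedom each for baseline and PEM, and a change of wording. Baseline ΔHR is measured and PEM status is recorded at randomisation, so no new data are needed. Enrolment has begun, so the change should go through the amendment route that the article describes, while the statistician is still blinded.

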Capnography: End-tidal carbon dioxide (EtCO₂) will be continuously monitored using a sidestream capnograph connected to a nasal cannula with an integrated sampling line. Measurements will be taken throughout the supine baseline period and during the upright tilt phase, with recordings synchronised with ECG and BP data. EtCO₂ values will be collected on a breath-by-breath basis and stored for offline analysis.^32^

Handgrip strength performance: Before and after the HUTT, participants will undergo a handgrip strength assessment using a CAMRY Digital Hand Dynamometer while seated. To evaluate muscle strength, fatigue and recovery capacity, a validated repetitive isometric handgrip strength protocol will be applied. Each participant will complete two rounds of a 10×3 s maximal isometric contraction test, separated by 1 hour. Within each round, participants will perform ten maximal contractions of 3 s each, with 5 s of rest between trials, paced by an interval timer. All measurements will be conducted in a seated position with the forearm supported and the hand in a neutral position.^33^

From this protocol, the following parameters will be calculated:

Maximum force (Fmax): The highest value of the 10 repetitions per round.Mean force (Fmean): Average of all 10 repetitions per round.Fatigue ratio: Fmax/Fmean of round 1. Higher values indicate greater force decline within a session (ie, higher fatigability).Recovery ratio: Fmean (round 2)/Fmean (round 1). Higher values reflect better recovery capacity between rounds.

This method allows for a more sensitive and objective evaluation of physical fatigue and recovery potential in older adults, beyond conventional HGS testing.

Activity and HR tracker: A wearable device (Fibion Flash) will monitor activity levels and HR for 3 days (2 nights) via ECG long-term adhesive electrodes at two points during the study: once in the first week and again after the 10th week of the intervention. This device provides a non-invasive, objective and real-time data collection method that tracks these metrics over an extended period. While the data are continuously collected and synced to a dedicated app or online portal, participants will not have access to real-time data such as HR, sleep, or activity levels to avoid influencing their behaviour. The collected data will be analysed by the research team.

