### Harms

Harms are defined as any AEs or side effects occurring during the trial, regardless of their causal link to the intervention. They will be assessed systematically through weekly AE questionnaires, supplemented by spontaneous reports from participants via phone, email or during visits. All events will be recorded in the case report form, including their severity, onset and duration. Discontinuation owing to AEs is permitted at any time, and reasons will be documented. Severe or concerning symptoms will prompt immediate contact with the study team. This structured monitoring ensures that both subjective complaints and objective safety concerns are consistently captured. The participant timeline and assessment schedule are detailed in figure 1.

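### The secondary-outcome models put a baseline covariate and a time-by-group term into one linear regression, and these parts do not fit together

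*Protocol article*

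**What the plan says.** Under Statistical methods, the protocol article states for the secondary outcomes (blood pressure, HRV, RSA, handgrip strength, patient-reported measures) that "linear regression models incorporating baseline values, age, sex and medication as covariates will be employed". It continues: "Interaction terms for time-by-group will be included to identify potential differences in trajectories over time". No random effect, residual covariance or robust standard error is named for these models.

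In the same paragraph the primary endpoint "will be analysed using repeated-measures ANOVA with Bonferroni correction applied to account for multiple comparisons", so a method for repeated measurements is named there. Of the primary endpoint the paragraph also says: "The main comparison will focus on the change in ΔHR from baseline to week 12 across the four intervention groups".

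On timing, the Harms section states: "The participant timeline and assessment schedule are detailed in figure 1". That figure is not shown in the text available. The activity tracker is worn "at two points during the study: once in the first week and again after the 10th week of the intervention".

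On status, the plan is explicit: "P values from secondary analyses will be considered exploratory and interpreted accordingly".

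**The concern.** A time-by-group term needs at least two outcome rows per participant. A baseline covariate belongs to a model whose outcome rows are all post-baseline. With one post-baseline value, the two can be combined only by also entering the baseline measurement as an outcome, so that it predicts itself exactly in half of the rows. Linear regression, in its plain meaning, also treats a participant's rows as independent.

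At stake are the standard errors, intervals and precision for the symptom, fatigue, quality-of-life and autonomic outcomes. If the wording stays, the analyst must also choose among several models later, possibly after seeing data.

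**Working it through.** The plan states no figure for the secondary models, so there is none to reproduce. The check concerns model form.

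**Inputs.** Model class, covariates and interaction come from Statistical methods. Group size is 25 recruited; for evaluable participants, the Sample size calculation section says "17 participants per group are required for sufficient statistical power". The within-person correlation ρ is not given, so 0.3, 0.5 and 0.7 are assumed. Outcomes have unit variance, equal correlation between visits and no true effect; n is the number per group.

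**Layout 1: week 12 as the only outcome.** There is one row per person and no time variable. The term is not estimable.

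**Layout 2: baseline and week-12 rows stacked.**

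1. The baseline covariate has the same value in both of a person's rows, so it cancels from the interaction. The estimate is the between-group difference in mean change, with true variance 4(1−ρ)/n.
2. The pooled slope on baseline is (1+ρ)/2. Residual variance is (1−ρ)²/4 in baseline rows and (1−ρ)(5+3ρ)/4 in week-12 rows. Their average is (1−ρ)(3+ρ)/4.
3. The regression therefore reports variance 4 × (1−ρ)(3+ρ)/4 ÷ n = (1−ρ)(3+ρ)/n.
4. Reported SE / true SE = √((3+ρ)/4), which is below 1 for every ρ < 1.
5. ANCOVA of the week-12 value on baseline has variance 2(1−ρ²)/n. The variance ratio is 4(1−ρ) / [2(1−ρ²)] = 2/(1+ρ).

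| ρ (assumed) | true variance × n | reported variance × n | SE ratio | implied type I error | ANCOVA variance × n | variance ratio to ANCOVA |
|---|---|---|---|---|---|---|
| 0.3 | 2.80 | 2.31 | 0.91 | 7.5% | 1.82 | 1.54 |
| 0.5 | 2.00 | 1.75 | 0.94 | 6.7% | 1.50 | 1.33 |
| 0.7 | 1.20 | 1.11 | 0.96 | 5.9% | 1.02 | 1.18 |

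A simulation agrees (4,000 runs per cell, four groups of 17 or 25). SE ratios were 0.89, 0.94 and 0.97–0.98. Rejection rates were about 8%, 6.3–6.6% and 5.7–6.2%. Week-12 ANCOVA had SE ratios of 1.00–1.02 and rejected 4.6–5.4%.

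Step 2 also shows unequal residual variance. At ρ = 0.5 it is 0.0625 in baseline rows and 0.8125 in week-12 rows, a 13-fold difference, although the plan says homoscedasticity will be checked.

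**Layout 3: two post-baseline visits, baseline as covariate only.** Baseline no longer predicts itself, but rows are still treated as independent. The regression uses residual variance 1−ρ².

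- *Interaction:* true variance 4(1−ρ)/n, reported 4(1−ρ²)/n. The SE ratio is √(1+ρ) = 1.14, 1.22 and 1.30, so SEs are too large. Simulated: 1.13–1.30, with type I error 1.1–2.9%.
- *Average group effect, no interaction:* true variance (1−ρ)(1+2ρ)/n, reported (1−ρ²)/n. The SE ratio is √((1+ρ)/(1+2ρ)) = 0.90, 0.87 and 0.84, so SEs are too small. Simulated: 0.85–0.90, with type I error 7.6–9.6%.

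**The case against.** **The data layout is inferred.** Change from baseline to week 12 is stated only for the primary endpoint. For secondary outcomes the plan speaks of trajectories, and the schedule figure is not shown. A reader might infer that baseline is definitely both predictor and outcome; the documents do not establish that. The text does lean that way: the contacts at weeks 2, 6 and 10 and the follow-ups every 2–3 weeks are described for retention and adherence, and no intermediate measurement of a secondary outcome is mentioned. The claim stays conditional.

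**A condensed article may leave the covariance structure to the analysis plan.** This is fair, and silence on covariance alone would be no finding. With several post-baseline visits, and if linear regression loosely meant a mixed model, the specification would be sound. But the article does state a model class, a covariate set and an interaction, and as stated they do not fit together. It also names a repeated-measures method for the primary endpoint in the same paragraph.

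**The mechanism can be overstated.** A reader might infer that the common slope on baseline biases the interaction. It does not: baseline cancels, and the slope affects only the residual variance and hence the SE. The precision loss is the familiar gap between change scores and ANCOVA. A stacked regression without the baseline covariate would be conservative, but the plan does not propose that model.

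**The impact is modest.** This stands. The inflation is small in the two-time layout, its direction differs between layouts, and the analyses are labelled exploratory.

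**Conclusion.** The point holds as a specification error in the exploratory secondary models. If baseline and week 12 are the only outcome times, the time-by-group term either cannot be estimated or requires baseline rows as outcomes. In the stacked case the estimate is unbiased, but its standard errors are about 4–9% too small, with type I error of about 6–7.5%. Its variance is 1.18 to 1.54 times that of ANCOVA. At ρ = 0.5, matching ANCOVA with 25 per group would take about 25 × 1.33 ≈ 33 per group. With several post-baseline visits the errors are those of Layout 3, and their direction depends on the effect tested.

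The sizes rest on assumed correlations of 0.3–0.7, equal correlation between visits, and linear regression meaning independent rows. It would go too far to conclude that all secondary p-values are wrong in one known direction, or that any confirmatory result is at risk. The layout is not confirmed, and the primary endpoint uses a different analysis that this point does not touch.

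**What to change.** State the outcome times for each secondary outcome and choose the model accordingly.

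- **Baseline and week 12 only:** ANCOVA of the week-12 value on baseline, the randomised factors (AVNT, SDB and their interaction), the covariates already listed (age, sex, medication) and PEM, the stratification factor named under Type of randomisation. Drop the time-by-group term.
- **Two or more post-baseline visits:** replace linear regression with a mixed model with participant-level covariance. Use baseline as a covariate (post-baseline rows only) or as an outcome, not both. The time-by-group term may then stay.

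The cost is a change of wording in the analysis section, best made before the data are unblinded. Sample size, visits and the primary analysis do not change.
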